### Intervention

All eligible patients with CAP who meet the ASP review criteria will receive the ASP intervention (ASP-i). This intervention consists of a prospective chart audit and physician feedback (persuasive) approach [25]. The ASP members who conduct all the audits and make recommendations consist of a pharmacist trained in infectious diseases (LM) and a physician trained in infectious diseases (GD). All patients are reviewed by both members. The ASP-i recommendations are guided by the Infectious Diseases Society of America CAP guidelines [1] and the Canadian Thoracic Society guidelines for the management of chronic obstructive pulmonary disease [26]. The possible ASP-i recommendations are based on those recommended by the UK National Health Service [25] and include:No change to current careDiscontinue antibioticsIntravenous to oral conversionDuration of therapyDosing changeNarrow or broaden spectrum of therapy.

The ASP-i recommendations are not mutually exclusive. All recommendations are documented in the patient’s electronic medical record and communicated directly to the attending physician by the ASP members.

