### Study design

This is a pragmatic controlled non-randomized clinical study intended to measure the effectiveness of a ‘real-world’ program [27]. The ASP-i will be implemented in a modified stepped-wedge design [28]. Baseline patient data will be collected for all enrolled patients on each of the medical wards for the first 3 months of the study, and then the ASP-i will be introduced to each medical ward in a non-randomized sequential fashion in 2-month intervals until all medical wards are exposed to the intervention. This design was chosen for several reasons; the preponderance of evidence suggests that antimicrobial stewardship interventions are beneficial to patient safety and quality of care [29]; there are human resource limitations in rolling out the program simultaneously to all wards; and the design has the advantage of a contemporaneous control group for comparison. The unit of randomization in this study could have been the four medical wards; however, randomization of the wards was not included in the design. The allocation of CAP patients to one of the four medical wards is controlled by bed allocation, an administrative branch of the hospital. Bed allocation was blinded to the study and the process of patient allocation is solely dependent on bed availability. In addition, the patients, regardless of their ward location, were all admitted to the hospitalist service. The hospitalist service provides coverage across all four medical wards and has no influence on the allocation of patients to any of the wards. In essence, the patients will be ‘naturally’ allocated to one of the four medical wards and one of the attending hospitalists by a bed allocation process that is blinded to the intervention, so that the additional randomization of the wards themselves should provide very little benefit with respect to minimizing selection bias. In addition, the four medical wards can all accommodate patients with CAP; however, one of the medical wards has historically accommodated more CAP patients than the other three. As a result, this ward was chosen as the first ward to receive the ASP-I, as this would ensure that the maximum number of CAP patients would have earlier access to the ASP-i. The ethical principle of utilitarianism was used to guide the order of ward exposure to the ASP-i. The target of the intervention is the most attending physician (hospitalist) , while the unit of analysis will be individual patient outcomes adjusted for potential clustering effects within hospital wards.

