### Participant timeline

Enrollment of patients started 1 April 2013. The study is expected to enroll patients until 31 March 2015. All consecutive patients who meet the inclusion criteria and have no exclusion criteria will be eligible for the intervention. The ASP-i intervention may be implemented any time from 48 hours after admission in those patients who meet the criteria for ASP review. All patients who have not experienced an outcome measure at 14 days after admission will be censored from the study. Patients who die or are transferred from the ward (to the intensive care unit or other hospital) will also be censored. Patients who are discharged from hospital and are not censored will be contacted 30 days after discharge to determine their adherence with antibiotic prescription (if relevant), survival status, and readmission status.

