### Statistical methods

An extended Cox regression analysis that models the ASP-i as a time-variant covariate will be used to compare the primary and secondary outcome measures between the control and intervention groups [34]. Violations of the proportional hazards assumption for each covariate will be identified using the method of Schoenfeld residuals combined with the graphical method of log-log survival curve analysis [34]. Results will be reported as hazard ratios with 95 % confidence intervals. Patients who remain in hospital beyond 14 days will be administratively censored. Competing events, such as death or transfer from a medical ward to a critical care unit will be assumed to be non-informative conditional on the covariates included in the final model [34]. Time to ASP-i will be modeled as a time-variant covariate in the final model to account for any time-dependent bias [23]. The ASP-i exposure will be coded as a dichotomous variable; 0 = no ASP-i, switching to 1 = ASP-i at the time of the ASP-i and remaining 1 throughout the remainder of the follow-up time. This method treats a patient who has received an ASP-i as a non-ASP-i patient prior to the intervention. Other variables known to be associated with the primary and secondary outcome measures will also be included in the final model [5], and include; age, sex, Charlson comorbidity index, CURB-65 score, time (days) to clinical resolution, and complications from pneumonia, such as empyema. Fixed effects of wards on the outcomes will accounted for by including them as indicator variables in the final model. Maturation of ASP-i effect on outcomes over time will be adjusted by including a categorical time variable in the final model (time variable will be defined as ‘quarter’ from start of study). A dichotomous variable for acceptance or rejection of the ASP-i will be part of an interaction term with the control/intervention group variable to permit a per-protocol analysis. Sensitivity analysis will be done using a competing events Cox regression model to determine the impact of the assumption of the non-informative nature of events, such as death and admission to an intensive care unit [35].

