This study has several challenges to its internal and external validity. First, the absence of medical ward randomization could introduce selection bias. However, the allocation of patients to the ward and their medical provider is determined through a ‘natural’ allocation process that is blinded to the study, thus minimizing this potential source of bias. Secondly, the ASP members are not blinded to the intervention, outcome measure assessment, or data analysis. However, the likelihood of introducing bias is minimal because the primary and secondary outcome measures are stringently defined and objective. Thirdly, the risk of contamination is significant given that the hospitalists provide coverage across the four medical wards. It is conceivable that their behaviour will change over time as they become conditioned to the ASP-i and that this behaviour change might then precede the ASP-i as the study evolves over the 2 year period. The consequence of this contamination would be to bias the outcome hazard ratios toward a value of 1 or no ASP-i effect. However, a recent Cochrane review of the impact of audit and feedback on physician behaviour demonstrated only a 4.3 % (interquartile range, 0.5 % to 16 %) absolute increase in adherence with best practice [42], suggesting that the risk of contamination in this study might be small given the inherent resistance of physicians to changes in behaviour. In addition, the rate of ASP-i consults per month (defined as the ratio of the number of ASP-i consults to the number of eligible patients) will be modeled as time series data, and an assessment using regression analysis and the Durbin alternative test will be used to detect any serial correlation between the previous months’ ASP-i and the subsequent rate of ASP-i consults. Evidence of serial correlation between preceding ASP-i and subsequent rates of ASP-i consults would suggest possible contamination. Of course, contamination in this study might simply represent that the ASP was able to effectively change physician behaviour in a positive manner; a desirable impact for patient care, albeit with some undesirable effects on exposure-outcome evaluation. Fourth, the timing of the ASP-i at ≥48 hours after admission restricts the option of recommending earlier conversions from intravenous to oral antibiotics in eligible patients. Previous studies have suggested that earlier conversions might reduce length of stay [31, 43]. If the causal mechanism for reducing length of stay is through this earlier conversion, then this study might not be able to detect this ASP-i effect. As a single hospital site study, the applicability of the results to other hospitals and programs is unknown. However, a multi-site study using the same design, intervention, and analysis is currently being planned. Submissions of the proposal have been made to each participating hospital’s research ethics board. The anticipated start date of this multi-site study is 1 May 2015.

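### The primary hazard ratio compares patients by receipt of an ASP review, but the stated protection against selection bias covers only a comparison by ward phase

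*Protocol article*

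**What the plan says.** **Allocation.** Under Study design, the ASP-i is "introduced to each medical ward in a non-randomized sequential fashion in 2-month intervals until all medical wards are exposed to the intervention", after a 3-month baseline. Ward order follows historical CAP volume. Randomizing the wards is judged to add little because bed allocation staff, blinded to the study, place patients by bed availability. The section adds that "the design has the advantage of a contemporaneous control group for comparison". The Discussion repeats the argument, describing a "process that is blinded to the study, thus minimizing this potential source of bias".

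**Who is reviewed, and when.** Participant timeline: "The ASP-i intervention may be implemented any time from 48 hours after admission in those patients who meet the criteria for ASP review". The Discussion tracks consults as "the ratio of the number of ASP-i consults to the number of eligible patients", so the plan does not take every eligible patient to be reviewed.

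**Exposure in the model.** Statistical methods sets a 0/1 covariate, "switching to 1 = ASP-i at the time of the ASP-i and remaining 1 throughout the remainder of the follow-up time", and adds: "This method treats a patient who has received an ASP-i as a non-ASP-i patient prior to the intervention". Ward and calendar quarter enter as indicators. The other covariates are age, sex, Charlson index, CURB-65, time to clinical resolution, and complications. No term represents the ASP phase of the ward.

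**The concern.** Two comparisons are being treated as one. Blinded bed allocation makes patients comparable between wards that have the program and wards that do not. It has no bearing on which patients within an active ward are reviewed, or on which day. The planned covariate measures the second.

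Whether and when a patient is reviewed depends on meeting the criteria and on the hospital course after 48 hours, and that course also predicts discharge. If review falls more often on slower patients, the hazard ratio for discharge is pulled below 1 and a benefit is hidden. If it falls more often on stable patients, the ratio is pushed above 1 and a benefit is manufactured. The Discussion lists several threats to validity; this one is not among them, and its case for the coding concerns time-dependent bias alone.

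**Working it through.** **1. The plan's own figure.** Sample size gives 400-500 patients a year for 24 months (N = 800-1000), 70% discharged alive, power 0.80 and two-sided α 0.05. The Cox power formula is |ln HR| = (1.960 + 0.842) / √[a(1−a) × 0.70 × N], where a is the exposed share. The article does not state a; I take 0.5.

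- N = 800: 2.802/√140 = 0.237, HR 0.789 (1.267)
- N = 900: 2.802/√157.5 = 0.223, HR 0.800 (1.250)
- N = 1000: 2.802/√175 = 0.212, HR 0.809 (1.236)

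The stated figure of about 20% reproduces, with balanced exposure and no loss for ward and quarter terms.

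**2. What the roll-out leaves to compare.** A 3-month baseline and 2-month steps put the ward starts at months 3, 5, 7 and 9, if the first ward starts when baseline ends. With equal ward volumes the share of patients on active wards is (21 + 19 + 17 + 15)/(4 × 24) = 75%. From month 9 every ward is active, so 15/24 = 62.5% of accrual (quarters 4 to 8) has no control-phase ward. Within those quarters the only exposure contrast is reviewed against not-reviewed patient-time.

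**3. Simulation with no true effect, prognosis not in the model.** Assumptions: 900 patients; about 72% discharged by day 14; ward shares 40/30/20/10%; review at 48 h plus a mean of 1 day; a binary recovery marker; criteria met by 85% of one marker group and 55% of the other; ward and quarter terms; 200 runs. HR above 1 means faster discharge.

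| Who tends to meet the criteria | Receipt-coded HR (null rejected) |
|---|---|
| Unrelated to recovery | 1.00 (6%) |
| Slower patients, marker HR 1.5 / 2 | 0.91 (17%) / 0.83 (47%) |
| Faster patients, marker HR 1.5 / 2 | 1.12 (21%) / 1.18 (39%) |

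Ward-phase coding gave 0.99-1.01 with 2-7% rejections throughout.

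**4. The same question with partial covariate adjustment.** Assumptions: 900 patients; prognosis SD 0.6 on the log discharge hazard; one measured covariate in the model capturing a stated share of prognostic variance; 100 runs per scenario (Monte Carlo error of a rejection rate at most √(0.25/100) = 5 points).

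| Odds ratio for review per SD | Share captured | Receipt-coded HR (null rejected) |
|---|---|---|
| 1.6, slower patients | 30 / 50 / 70% | 0.90 (16%) / 0.92 (13%) / 0.95 (10%) |
| 2.0, slower patients | 25 / 50% | 0.85 (36%) / 0.89 (20%) |
| 2.7, slower patients | 30 / 50 / 70% | 0.80 (56%) / 0.85 (33%) / 0.90 (17%) |
| 2.0, stable patients | 25 / 50% | 1.17 (33%) / 1.12 (15%) |

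A further run with 30-50% captured gave 0.84-0.93 or 1.10, with 12-37% rejections. Where it was fitted, ward-phase coding gave 0.99-1.01 with 4-7% rejections.

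Against the design effect (ln 1.25 = 0.223), a spurious 1.10-1.17 is 0.095/0.223 = 43% to 0.157/0.223 = 70% of it, and a spurious 0.80 cancels it.

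**5. Precision.** The simulated SE of ln HR is about 0.10 for receipt coding. For ward-phase coding it is about 0.16 when exposure switches on at 48 h and about 0.19 when it is coded from admission. Detectable HR = exp(2.802 × SE): 1.32 at 0.10, 1.57 at 0.16, 1.70 at 0.19. Power for HR 1.25 is Φ(0.223/SE − 1.96): about 29% at 0.16 and 22% at 0.19.

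**The case against.** The strongest reply is that the final model does adjust for prognosis, that the review rule and reviewed fraction are not in the article, and that receipt coding answers a legitimate question: the effect of delivered audit and feedback.

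Much of this stands. Adjustment shrinks the bias, as step 4 shows, and if meeting the criteria is unrelated to recovery there is none (step 3, first row). Leaving the criteria to a fuller protocol is normal for an article. But age, sex, Charlson index and CURB-65 do not follow the course after 48 hours. Time to clinical resolution and complications can arise after the review, so adjusting for them may introduce bias of its own.

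A reader might infer two stronger things. One is that the stepped-wedge allocation goes unused. It does not: the roll-out decides who can be exposed, control-phase patients supply unexposed time, and ward and quarter are in the model. What is missing is an exposure contrast by ward phase. The other is that the planned model will miss by the amounts seen when prognosis is left wholly unadjusted. Those are no-adjustment extremes under an assumed review mechanism, not a description of this plan.

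The group variable named in the per-protocol interaction might be a ward-phase indicator, but it is not defined and serves only that interaction.

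**Conclusion.** The concern holds as a mismatch between the stated protection and the planned estimate. The receipt-coded hazard ratio is an as-treated comparison, open to confounding by indication, and bed allocation does not protect it. The time-varying coding is right for immortal time and should not be criticized on that ground.

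Neither size nor direction can be established from the article. The ranges of 0.80-0.95 and 1.10-1.17 rest on assumed review odds ratios of 1.6-2.7 per SD and on a covariate capturing 25-70% of prognostic variance. They show that a bias comparable with much of the design effect is possible, not that it will occur. The near-1.0 result for ward-phase coding assumes that bed allocation works as described. The simulations include no ward-specific time trends and no contamination through hospitalists who cover all wards, so the ward-phase precision is, if anything, optimistic.

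**What to change.** - **Add a ward-phase (intention-to-treat) analysis.** Code 0 for everyone up to 48 h after admission, then 1 for every eligible patient admitted to an active ward, reviewed or not, with ward and quarter terms. This keeps the protection against time-dependent bias. Make it primary if possible; otherwise report it beside the receipt-coded model.
- **Label the receipt-coded hazard ratio** as an as-treated estimate subject to confounding by indication.
- **Limit the selection-bias statements** in Study design and the Discussion to the ward-phase contrast, and state that no control-phase ward remains from month 9.
- **Restate the power.** The figure of about 20% does not apply to the ward-phase analysis, whose detectable hazard ratio is about 1.6-1.7.

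No new data are needed: ward and admission time are already recorded. The real cost is statistical. The ward-phase effect is diluted by unreviewed patients and much less precise, and it estimates the effect of introducing the program rather than of a delivered review. Because 582 patients are already enrolled and the principal investigator both analyses the data and prepares quarterly outcome reports, the change should be dated and documented, with a note of which results had been seen.

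### The quarter-from-start term adjusts for secular trend, not for maturation of the ASP-i effect as stated; the single hazard ratio stays constant over programme time and can understate an effect that grows.

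*Protocol article*

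**What the plan says.** All the model terms are in the Statistical methods section of the protocol article.

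- **Time.** "Maturation of ASP-i effect on outcomes over time will be adjusted by including a categorical time variable in the final model", with the definition "time variable will be defined as ‘quarter’ from start of study".
- **Exposure.** "The ASP-i exposure will be coded as a dichotomous variable; 0 = no ASP-i, switching to 1 = ASP-i at the time of the ASP-i". It then stays at 1 for the rest of follow-up.
- **Ward.** "Fixed effects of wards on the outcomes will accounted for by including them as indicator variables in the final model".
- **Interactions.** One only: "A dichotomous variable for acceptance or rejection of the ASP-i will be part of an interaction term with the control/intervention group variable".

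The Study design section sets the calendar. "Baseline patient data will be collected for all enrolled patients on each of the medical wards for the first 3 months of the study"; the programme is then introduced in a "non-randomized sequential fashion in 2-month intervals until all medical wards are exposed to the intervention". The Participant timeline section allows review from 48 hours after admission, in patients who meet the review criteria, and censors at 14 days. The Sample size section gives 24 months of accrual.

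**The concern.** Maturation of an effect means that the ASP-i works better, or worse, as the programme ages. A model can represent that only if the ASP-i coefficient may differ by programme time. A quarter indicator entered as a main effect multiplies the discharge hazard by the same factor for reviewed and unreviewed patient-time in that quarter. It removes drift common to both, which is worth doing, but it does not touch the ASP-i coefficient.

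Two things are at stake. Readers would be told that maturation had been handled when the model assumes there is none. And if the effect does grow, some of the growth can be credited to the quarter terms and not to the ASP-i. The primary HR is then pulled down, most of all when few unreviewed patients remain in the later quarters as comparators.

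**Working it through.** **1. What the model can represent.** From the stated terms, the log hazard of discharge is

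log h(t) = log h0(t) + ward + quarter + β·ASP-i(t) + patient covariates,

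with the acceptance interaction added for the per-protocol analysis. Within any ward and quarter, reviewed against unreviewed is β. The quarter term cancels, so β is the same in every quarter. The Schoenfeld-residual check does not cover this, because it examines proportionality over time since admission (up to 14 days), not over programme time.

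**2. Calendar.** A 3-month baseline and 2-month steps put the ward starts at months 3, 5, 7 and 9. All four wards are active for 24 − 9 = 15 of 24 months. A study quarter during roll-out therefore mixes wards of different programme age.

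**3. The plan's own figure, for scale.** The Sample size section gives 400-500 patients a year, hence 800-1,000 over 24 months, with 70% discharged alive, 80% power and two-sided α of 0.05. The Schoenfeld formula with equal allocation (an assumption; no split is stated) is HR = exp[2 × (1.96 + 0.84) / √D].

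- D = 560: 1.267
- D = 630: 1.250
- D = 700: 1.236

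Since 1/1.25 = 0.80, the stated reduction of about 20% reproduces. This point does not affect it.

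**4. What the planned model returns if the effect grows.** From the documents: the ward starts, 24 months of accrual, 70% discharged by day 14, and ASP-i switching from 0 to 1 no earlier than 48 hours. Assumed: ward shares 40/25/20/15%, reviewed patients otherwise like unreviewed ones, review at exactly 48 hours or after a further mean delay of 1 day, and a log-HR rising linearly from 0 to 0.30 over 12 months on each ward. The mature HR is exp(0.30) = 1.35. The average over exposed person-time is 1.22. Fitting a piecewise-exponential equivalent of the Cox model (day, ward, quarter and one ASP-i term) gives:

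| Eligible patients reviewed | HR, review at 48 h | HR, mean 1-day delay |
|---|---|---|
| 100% | 1.12 | 1.17 |
| 90% | 1.18 | 1.19 |
| 80% | 1.20 | 1.21 |
| 70% | 1.21 | 1.21 |
| 60% | 1.21 | 1.22 |

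A separate large simulation of the same scenario agrees to about 0.01.

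**5. Other growth sizes and a control.** In 400,000-patient simulations of the same design, with linear growth over 12 months:

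| Mature HR | Average HR | 100%, 48 h | 100%, 1-day delay | 80%, 1-day delay | 60%, 1-day delay |
|---|---|---|---|---|---|
| 1.25 | 1.16 | 1.09 | 1.13 | 1.14 | 1.16 |
| 1.50 | 1.31 | 1.15 | 1.23 | 1.29 | 1.31 |

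With a truly constant HR of 1.25 the planned model returns 1.24-1.27, so the shortfall comes from the growth. Replacing the single term by one ASP-i term per quarter since ward roll-out (mature HR 1.25, all reviewed at 48 h) recovers the growth: 1.03, 1.08, 1.16, 1.22, 1.26, 1.27, 1.25.

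**6. Consequence for power, roughly.** At 630 events with equal allocation, z = ln(HR) × √(630 × 0.25) − 1.96 = 12.55 × ln(HR) − 1.96.

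- HR 1.22: z = 0.54, power about 70%
- HR 1.20: z = 0.33, power about 63%
- HR 1.17: z = 0.01, power about 50%
- HR 1.12: z = −0.54, power about 30%

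**The case against.** **The loss depends on coverage and may be small.** This stands. Exposure is coded per patient and starts no earlier than 48 hours, so every late quarter still contains unexposed person-time: the first two days of each stay, delayed reviews and unreviewed patients. At 60-80% reviewed the planned HR is within about 0.02 of the average.

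**A reader might infer that the model would nearly erase a growing effect.** If exposure were coded by ward phase, with every patient on an active ward exposed from admission, a simple projection of the same growth scenario gives 1.01 against an average of 1.23. The article does not plan that coding, and under the planned one the result stays at 1.12 or above even at full coverage.

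**A reader might infer that the plan predicts maturation.** The Discussion speaks of hospitalists, saying that "their behaviour will change over time as they become conditioned to the ASP-i". But that sentence presents the change as conceivable only, the text goes on to suggest that the risk might be small, and the process described is contamination: changed behaviour that precedes the review and biases the HR toward 1. It is not an ASP-i effect growing with exposure. The case here rests on the Statistical methods sentence alone.

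**Time since ward roll-out is not the only sensible clock.** This stands. Hospitalists cover all four wards and the same two ASP members do all the reviews, so learning may be hospital-wide. Using study quarter is not in itself an error.

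**The article is condensed, and an average HR is a legitimate primary target.** Both are fair. That quarter is a main effect is inferred, although the explicit naming of one interaction makes it much the likelier reading. Wanting a single average HR is a reason to keep the primary model, not a reason to say that it adjusts for maturation.

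**Conclusion.** The statement is wrong as written. The term described adjusts for secular trend, and the ASP-i HR remains constant over programme time. That follows from the model terms and needs no assumption beyond reading quarter as a main effect.

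The numerical consequence is conditional. In the growth scenarios of step 4 the reported HR (1.12-1.22) is always below the mature HR (1.35). It is clearly below the average (1.22) only when nearly everyone eligible is reviewed: 1.12-1.17 at 100% and 1.18-1.19 at 90%. At 60-80% it is 1.20-1.22, close to the average. If the effect waned from the same starting size to zero over 12 months, the error would reverse: 1.12-1.15 against an average of 1.10 at 70-90% reviewed. Coverage, ward shares, effect size and the shape and length of growth are all assumed.

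This warrants a correction of the text and a supplementary analysis. It does not warrant replacing the primary model or revisiting the sample size.

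**What to change.** 1. Keep the quarter variable, describe it as adjustment for secular trend, and delete the statement that it adjusts for maturation of the ASP-i effect.
2. Prespecify a supplementary model in which the ASP-i term varies by programme time, for example 0-3, 3-6 and over 6 months since that ward's roll-out. Repeat it with hospital-wide time since the first roll-out as the alternative clock.
3. Report the period-specific HRs and their average over exposed person-time next to the single primary HR, together with the proportion of eligible patients reviewed in each quarter, since that determines how far the single HR can drift from the average.

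The model needs only roll-out, admission and review dates, which the planned analysis already uses. The downside is precision: with about 560-700 events, the period-specific HRs will have wide intervals, so they should be presented as supportive.

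### Wards join every 2 months but the model adjusts calendar time in 3-month quarters, so a small part of any trend within two of the quarters leaks into the ASP-i hazard ratio

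*Protocol article*

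**What the plan says.** The Study design section sets the roll-out. "Baseline patient data will be collected for all enrolled patients on each of the medical wards for the first 3 months of the study"; after that the intervention is "introduced to each medical ward in a non-randomized sequential fashion in 2-month intervals until all medical wards are exposed to the intervention". There are four wards, and their order is not randomised. The same section gives as a reason for the design that "the design has the advantage of a contemporaneous control group for comparison".

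The Statistical methods section sets the model. Wards are handled by "including them as indicator variables in the final model". Calendar time enters once: "Maturation of ASP-i effect on outcomes over time will be adjusted by including a categorical time variable in the final model", and the "time variable will be defined as ‘quarter’ from start of study". No finer time term is named. The exposure is coded for each patient: "0 = no ASP-i, switching to 1 = ASP-i at the time of the ASP-i and remaining 1 throughout the remainder of the follow-up time".

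**The concern.** In a stepped roll-out, exposure and calendar time rise together. The time term has to separate the intervention from whatever else changes over the same months, such as seasonal illness, bed pressure or discharge practice. It does this fully only if no ward changes status inside a time period. With 2-month steps and 3-month quarters, some wards do.

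The article presents the quarter term as an adjustment for maturation of the effect. As a main effect it is also the model's only protection against secular trend. The misfit falls in the quarters that carry the comparison between active and inactive wards, and the ward order is fixed by design, so randomisation gives no protection. What is at stake is a bias in the primary hazard ratio of unknown sign, whose size has to be worked out.

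**Working it through.** **Stated figure first.** The Sample size section gives 400–500 patients a year for 24 months, 70% discharged alive, power 0.8, two-sided α 0.05, and a detectable effect of about 20%. With ln HR = (1.960 + 0.842) / √(events × 0.5 × 0.5), where an exposed share of 0.5 is assumed:

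| Patients | Events (70%) | Detectable HR | 1/HR |
|---|---|---|---|
| 800 | 560 | 1.267 | 0.789 |
| 900 | 630 | 1.250 | 0.800 |
| 1,000 | 700 | 1.236 | 0.809 |

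This is a reduction of 19–21%, so the figure reproduces. A hazard ratio of about 1.25 is the yardstick below.

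**Schedule against quarters.** Enrolment starts on 1 April 2013. Assuming the first ward goes live when the baseline ends, go-live is after months 3, 5, 7 and 9. Quarters end after months 3, 6, 9 and so on.

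| Quarter | Active wards |
|---|---|
| 1 (Apr–Jun 2013) | none |
| 2 (Jul–Sep 2013) | ward 1 throughout; ward 2 in September only |
| 3 (Oct–Dec 2013) | wards 1 and 2 throughout; ward 3 from November |
| 4–8 (Jan 2014 on) | all four |

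Number the months within a quarter 0, 1, 2. In quarter 2 the active ward-months are 1, 1, 2 (mean 5/4 = 1.25) and the inactive ones 3, 3, 2 (mean 7/8 = 0.875). In quarter 3 the active ones are 2, 3, 3 (mean 9/8 = 1.125) and the inactive ones 2, 1, 1 (mean 3/4 = 0.75). In both, active ward-time is 0.375 month later. The other six quarters have no contrast between wards, so trends inside them do not leak through the roll-out.

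**Ward-level leak.** A linear monthly trend was projected on ward ASP-i status with ward indicators and each time term (4 wards × 24 months). The entries show how many months' worth of slope the ASP-i coefficient absorbs.

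| Time term | Equal wards | Assumed shares 40/25/20/15% |
|---|---|---|
| none | 12.0 | 12.0 |
| quarter | 0.444 | 0.425 |
| month, or 2-month steps | 0 | 0 |

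Quarters remove 1 − 0.444/12.0 = 96% of the bias from a linear trend. Residual exposure variance with month terms falls from 0.0469 to 0.0434 (equal wards) or from 0.0442 to 0.0413 (unequal), a loss of about 7%.

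**Leak under the planned coding.** The exposure in the plan is not ward status but a patient-level switch, at 48 hours or later and only in patients who meet the review criteria. A noise-free Poisson model with hospital-day effects stands in for the Cox model. It has 14-day censoring, 70% discharged by day 14 and a true HR of 1.00. Assumed: 50–100% of patients reviewed, with audits spread over days 2–4 (50/30/20%). The fitted ASP-i HR with quarter indicators is:

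| Assumed trend in discharge hazard | Spurious HR |
|---|---|
| about 1% per month | 1.0004–1.0017 |
| about 3% per month | 1.001–1.005 |
| seasonal swing ±0.2 in log hazard, phase varied | about 0.99–1.01 |

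Month indicators return 1.000 for each of these trends. The seasonal result can go either way, depending on where the peak falls. The largest values come with every patient reviewed. If, in addition, every audit fell exactly on day 2, 3% per month would give 1.008 and the seasonal swing about ±2%. The standard error of the log HR is about 0.10–0.14 at 900 patients, and month terms widen it by about 1% or less (somewhat under 2% in the day-2 case).

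**The case against.** The strongest reply is that this is too small to matter. Quarters already take out nearly all of a linear trend, patient-level coding dilutes what remains, and case mix is partly adjusted directly through age, sex, Charlson index and CURB-65. The spurious shift is a small fraction of both the standard error and the detectable effect. This stands, and it sets the priority.

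A reader might infer that any drift within a quarter is credited to the ASP-i. It is not: only trends in quarters 2 and 3 leak through the roll-out, and only in part.

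A reader might also multiply the ward-level leak by a steep drift: 0.44 × 5–10% per month gives a 2–4% shift. The documents give no such drift, which would raise the discharge hazard 1.05⁹ = 1.55-fold to 1.10⁹ = 2.36-fold over the first nine months alone. Nor is ward status the planned exposure. Under the patient-level coding those drifts give about 1.002–1.013. They reach 1.020–1.026 only at 10% per month with every patient reviewed and audited from day 2.

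Finally, a reader might conclude that valid controls exist only in July–December 2013, so that a separate April–December 2013 estimate is needed. Inactive wards do exist alongside active ones only in those months. But the model also uses unexposed time on every ward throughout: time before the audit, and patients who do not meet the review criteria. A restricted estimate does not follow from mismatched periods. It would rest on 9/24 of accrual, about 300–375 patients.

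**Conclusion.** The mismatch is real and stands in the text: 2-month steps, 3-month quarters and no finer time term. On the inferred schedule it lets a small part of any trend within quarters 2 and 3 into the ASP-i hazard ratio, about 0.1–0.5% for a 3% monthly trend and about 1% in either direction for a ±0.2 seasonal swing. By itself this would not change a clear result.

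The size rests on assumptions that the documents do not fix: the first go-live date, the trends, the ward shares, the share of patients reviewed and the day of audit. If the first ward went live at month 5 instead, three of the four switches would fall inside a quarter and the ward-level leak would be 0.64–0.69 of a month's slope. The detectable effect in the Sample size section is not affected. Low priority, but worth doing because the remedy costs so little.

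**What to change.** In the Statistical methods section, define the categorical time variable as calendar month of admission (24 levels), or as periods matched to the roll-out: the 3-month baseline, the three 2-month steps to month 9, and then any convenient width, since no ward switches after that. Keeping quarters from month 9 gives 1 + 3 + 5 = 9 levels against the present 8. State the actual go-live dates, so that readers can see that no switch falls inside a period.

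Month terms add 24 − 8 = 16 parameters against about 560–700 discharges. The price is about 7% of the information in a ward-level model, or a standard error about 1% wider or less under the planned coding. No new data are needed, and no separate estimate for April–December 2013.
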